**Fig. 4 Fig4:**
[figure not shown]
Study flowchart

### Trial setting

The trial will take place in Luzhou, a city of Sichuan province in China. Luzhou, with a registered population 5.08 million, located in the southeast of Sichuan Province, is an adjacent city of four province Sichuan, Yunnan, Guizhou, and Chongqing. It is the area where the HIV/AIDS epidemic is rising rapidly in Sichuan Province [21]. Since the first HIV infection was found in Luzhou in 1996, a total of 4688 cases of HIV infection/AIDS were reported from 1996 to 2016, and 49.9% of them were aged ≥ 50 [22].

### Recruitment of participants

We will recruit 450 older men in multiple communities through on-site recruitment. In order to keep the baseline consistent, we have purposefully pre-selected three towns, Fangshan, Jiangbei, and Kuangchang. They are the most representative and have basically the same economic, cultural, and population levels in Luzhou city. In Chinese administrative divisions, each town contains 10–20 communities. In order to facilitate the implementation of intervention, two or three communities will be selected using simple random sampling from each town, and a total of 150 older men will be recruited from these communities in one town. The trial will be held in the residents’ activity centers of three communities (Fangshan community of Fangshan Town, Kuangchang community of Kuangchang town, and Jiangbei community of Jiangbei town).

Participants who sign up will be screened; for those who meet the inclusion criteria, we will issue informed consent to them and inform them in detail of the study purpose and process, number of participants, study duration, potential risks and benefits, random allocation, data confidentiality, etc. All information and written notices will be in Chinese. When the participants agree to join in the research and complete the follow-up measurement, an informed consent form will be signed for confirmation. If the participant is unable to read, the staff will read the informed consent to the participant in full and the participant will mark his or her own fingerprint to express consent; the entire process must be witnessed by a third party not involved in the trial.

To be eligible for trial participation, individuals must meet all the following inclusion criteria:
Male aged over 60 years oldClear consciousness, no mental illness and serious visual impairment, have certain reading ability and language expression abilityPlans to stay in the trial catchment area for over 6 months

Exclusion criteria include any of the following:
Ongoing or already on HIV education interventionCognitive and mental impairment and inability to communicate properlyImpaired vision or blind

The drop out criteria includes any of the following:
Have a serious illness during the experimentDeathOther irresistible factors, for example, infectious disease isolation

For these dropouts, i.e., those not reaching endpoint, will be counted as failures but analyzed intention-to-treat. It will be counted as having the average score on knowledge score, behavior attitude score, and the stigma scale.

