## Intervention group overview

### *Sunset Without AIDS* intervention group

Participants in the *Sunset Without AIDS* intervention group will receive a 25-min intervention. They will be required to watch the *Sunset Without AIDS* video once per week for 2 weeks. During the broadcast, a member of research team will be responsible for answering questions. After 2 weeks of intervention, the effect of the intervention will be evaluated using the same questionnaire as applied in the baseline survey.

To ensure the compliance of participants, participants will be recognized and rewarded after completing two video viewing sessions and 2-week follow-up assessments.

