### Statistical analyses

All questionnaires will be administered at baseline, and the final analyses will be adjusted for the baseline scores. Descriptive statistics will be used to show the baseline characteristics of each arm. The outcome measure (HIV-related knowledge, HIV-related behaviors attitude, and HIV-related behaviors) is a binary variable, and it will be compared by chi-square tests among the three arms at 2 weeks later and 1, 3, and 6 months of follow-up. To measure the HIV-related stigma attitude outcome, analysis of variance (ANOVA) will be used to find out whether there are differences among the three arms after 2 weeks of intervention. Repeated measures ANOVA will be used to measure the HIV-related stigma attitude score at 1, 3, and 6 months of follow-up. A Bonferroni correction will be used for multiple testing. Intention-to-treat analysis will be used to account for the influence of attrition. *P* ≤ 0.05 will be deemed statistically significant. All analyses will be performed using SPSS software.

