## Limitations

As with any research design, the trial also has potential limitations. In the follow-up observation, the time may be too long to lead to participant loss. We attempted to address this concern by giving each person some prizes to motivate the participants to continue to participate in the study. In addition, if necessary, participants can be traced through the information about the participants set aside on the informed consent.

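### Serious illness and isolation are drop-out criteria in themselves and carry replacement scores, and the protocol does not say that these men are still assessed or that their observed scores are used

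*Protocol article*

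**What the plan says.** The list under Recruitment of participants opens with "The drop out criteria includes any of the following", so one item is enough. The items are serious illness during the experiment, death, and other "irresistible factors, for example, infectious disease isolation".

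The next sentences attach the consequence: "For these dropouts, i.e., those not reaching endpoint, will be counted as failures but analyzed intention-to-treat". They continue: "It will be counted as having the average score on knowledge score, behavior attitude score, and the stigma scale".

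Teaching is short in every arm. The intervention group watches the "video once per week for 2 weeks", and the normal video and lecture groups follow the same two-session schedule. Under Assessments, the same interviewer-administered questionnaire is given after the 2 weeks of intervention and again at 1, 3 and 6 months. The primary outcome, a ten-item knowledge score, is due at all four (Outcomes and data collection; Table 3).

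Statistical analyses states: "Intention-to-treat analysis will be used to account for the influence of attrition". Limitations adds that, if necessary, "participants can be traced through the information about the participants set aside on the informed consent".

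**The concern.** In a trial of long-term treatment, a drop-out criterion can mark the end of treatment. Here teaching ends after the second session. From then on there is nothing left to drop out of except measurement. A man isolated around the 1-month visit may be able to answer ten knowledge questions at 3 and 6 months. A man too ill for the second session can be interviewed later if he recovers. If the list is applied as worded, both become dropouts and receive a substitute score.

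The promised intention-to-treat analysis is then met only in part: the man stays in the denominator of his arm, but his own obtainable outcome does not enter. What is at stake is information on the primary outcome, and reliance on replacement values for men who need none.

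**Working it through.** **1. The passages side by side**

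| Question | What the protocol gives |
|---|---|
| Is one event enough to be a dropout? | Yes, any item on the list |
| What happens to a dropout's scores? | Counted as a failure and given an average score |
| Is he still invited to later visits? | Not stated |
| Are scores he does give used? | Not stated |
| Does a missed visit differ from the end of follow-up? | Not stated |
| Is there teaching after week 2? | No, only questionnaires |

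**2. The possible readings**

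- *List as a rule:* a man isolated at 1 month is a dropout. His 3- and 6-month scores, though obtainable, are replaced.
- *List as reasons for a missing endpoint:* only the 1-month score is replaced. The wording permits this, but there are four assessments and the text does not say which of them is the endpoint that he failed to reach.
- *Illness item limited to the two teaching weeks:* illness after week 2 falls outside the rule, but a man ill in week 1 would have all four post-baseline scores replaced. The isolation item carries no such limit.

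**3. The plan's own sample size**

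Sample size and adherence gives 135 per group for 80% power, raised to 150. The step is consistent with 10%: 135/(1 − 0.10) = 150. The 135 cannot be reproduced because no effect size, SD or rates are given.

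**4. Size, as an illustration**

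Assumptions: two arms compared on the mean score, two-sided 5% level (sidedness is not stated), normal approximation.

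The difference that gives 80% power at 135 per arm is d = (1.960 + 0.842) × √(2/135) = 0.341 SD.

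Power at n observed per arm is Φ(0.341 × √(n/2) − 1.960):

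- n = 135: Φ(0.842) = 80%
- n = 143 (about half of the 15 kept): Φ(0.923) = 82%
- n = 150 (all kept): Φ(0.993) = 84%

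The protocol gives no rate of illness or isolation, so a range is shown for the share per arm whose scores are lost:

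| Share lost | Observed per arm | Power |
|---|---|---|
| 0% | 150 | 84% |
| 2% | 147 | 83% |
| 5% | 142.5 | 82% |
| 10% | 135 | 80% |
| 20% | 120 | 75% |

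**5. What the replacement value adds**

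This belongs to a separate defect: the failure rule and the average rule conflict, and the average is not defined. At an assumed share m = 10% replaced:

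- One common average keeps 1 − 0.10 = 90% of the difference.
- An own-arm average leaves the difference alone but understates its error. Type I error becomes 2 × [1 − Φ(1.96 × 0.90)] = 7.8%.
- Counting as failures turns an assumed 50% versus 67% into 45% versus 60.3% (each × 0.90). Power at 150 per arm falls from 85% to 76%. Losing the same 15 men with no replacement (135 per arm) gives 81%, so 5 of those 9 points come from the replacement rule.

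**The case against.** The strongest reply is that the text never says visits stop. It glosses dropouts as men who do not reach the endpoint, so the list may simply name reasons for missing data. The Introduction calls the intervention a 2-week experiment, which would confine the illness item to the teaching period. Prizes at each assessment, 50 RMB on completion and the tracing provision all point toward keeping men in. Dropouts remain in the analysis, and a condensed article may leave finer detail to the full protocol.

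Much of this stands. A reader might infer that the plan stops measuring these men or openly breaches intention-to-treat. The documents do not support that: they are silent on continued assessment, and the men stay in their arms. Nor is isolation described as temporary, and with face-to-face interviews some ill or isolated men will be unobtainable.

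It does not remove the point. The difficulty is a rule that is stated, with a consequence attached, rather than detail left out. No sentence says that observed later scores of these men count. The tracing provision is offered for participant loss in general and is not linked to this rule. The narrower readings are possible, but the text does not choose among them.

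The objection on size is also fair. The 135-to-150 margin is attributed to secondary outcomes and attrition, and Table 2 lists a 10% increase under contamination and fidelity. Nothing says that 15 men per arm will meet these criteria.

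**Conclusion.** The point holds as a defect in a stated rule and should be corrected. The list and its consequence, read as written, replace knowledge scores that could be collected, and the endpoint clause does not settle the matter across four assessments.

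The effect is moderate. If the whole margin of 15 per arm met the criteria, keeping half or all of them would move power from 80% to about 82% or at most 84%. The upper figure is a ceiling, because death is on the list and those scores cannot be obtained. At smaller shares the gain is smaller. All of this rests on an effect back-solved from 135 per arm and an assumed share affected.

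Two larger claims should not be drawn. The fall from 85% to 76% is not the cost of this rule alone, since part of it comes from counting men as failures and the rates are assumed. Movement of the arms toward each other follows from counting as failures or from a common average, but not from an own-arm average. Confidence is medium, because the narrower readings cannot be excluded.

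**What to change.** Under Recruitment of participants, replace the drop-out list and the sentences on dropouts with a follow-up rule:

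- Meeting a listed criterion, missing a session or missing a visit does not end follow-up. Follow-up ends only at death or withdrawal of consent to be contacted.
- Men are invited to every remaining scheduled visit, using the tracing details described under Limitations.
- Every observed score is analysed in the randomised arm.
- Replacement is confined to scores truly missing at that visit.
- Reasons for missing visits are recorded by arm.

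Which replacement value to use is to be settled separately. The cost is protocol wording and a few more contact attempts for visits that are already scheduled. This is a data-collection rule and changes nothing in the management of participants.

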### Sample size and adherence

The sample size calculation is based on the primary outcome, i.e., HIV-related knowledge. The sufficient statistical power to detect changes in HIV-related knowledge after the intervention were considered in sample size calculation, and 135 participants were need in each group to maintain 80% statistical power. Considering this sample size was also powered for the secondary outcomes and the attrition rate, the sample size of each group was determined to be 150, and the total sample size was 450.To motivate participants to stay in the trial, we would use intrinsic reward to help 450 participants adhere to the intervention and follow-up. Participants would receive some prizes for each assessment. In addition, after completing the research, each participant would also receive a reward of 50 RMB in cash.

### Randomization and allocation concealment

Individual randomization will be used in allocation. Participants will be randomly assigned to one of the three intervention groups on a 1:1:1 basis. Opaque envelopes will be prepared for randomization. In 450 envelopes, each will contain a note with the words “*Sunset Without AIDS* intervention group” or “Normal video group” or “Lecture group” (150 envelopes per group). A statistician will be responsible for the generation of random sequence numbers and place them on a sequential list that will be maintained by the trial coordinator. Participants (*n* = 450) will be randomly assigned a computer-generated random number from 1 to 450, and they will randomly select an envelope in the numbering order. For each envelope selected by participants, the total number of envelopes will be reduced by one until all 450 are achieved. Participants will be randomly allocated to the different groups with a closed envelope and supervise from a third party. Separate research staff will record the allocation information of the participants. Another staff will assign participants to interventions. These staff members were not involved in the data collection and analysis process. The data analysts are blinded to the allocation. All interviewers are not involved in delivering the intervention, so they will also remain blinded.

## Intervention group overview

### *Sunset Without AIDS* intervention group

Participants in the *Sunset Without AIDS* intervention group will receive a 25-min intervention. They will be required to watch the *Sunset Without AIDS* video once per week for 2 weeks. During the broadcast, a member of research team will be responsible for answering questions. After 2 weeks of intervention, the effect of the intervention will be evaluated using the same questionnaire as applied in the baseline survey.

To ensure the compliance of participants, participants will be recognized and rewarded after completing two video viewing sessions and 2-week follow-up assessments.

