### Normal video group

Participants in the normal video group will receive a 25-min of HIV education video intervention downloaded from the website of the Chinese CDC. And it is a popular science propaganda video, which lacks a storyline and is not specifically aimed at older people. Video length time and duration are the same as the *Sunset Without AIDS* group. The video contains the similar educational contents as the *Sunset Without AIDS*.

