### Lecture group

Participants will receive health education lecture related to AIDS once a week for 25 min each time. An AIDS expert will hold a health lecture on AIDS prevention, and the educational content of the lecture is the similar as that in the videos. The whole lectures will be carried out once a week for 2 weeks.

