By evaluating a brief video-based, scalable and locally developed and culturally tailored tool for improving HIV prevention in older men, three arms were designed in this trial, including one intervention arm and two control arms. To critically examine the implementation of *Sunset Without AIDS*, we will also examine participant satisfaction, intervention fidelity, contamination, and time-motion data. By comparing the intervention group with the normal video group, it can be found whether the *Sunset Without AIDS* is attractive and is better than a popular science propaganda video in improving (participants’) AIDS prevention ability. By comparing the intervention group and lecture group, we can figure out whether only a brief video-based intervention is different from a traditional health lecture intervention. By comparing each group before and after the intervention, we can see the difference in the effect of video-based interventions and health lecture intervention in AIDS education. This randomized controlled trial will critically evaluate this video-based intervention to improve the ability of AIDS prevention in older men. It will provide an evidence for the choice of AIDS education methods for older men.

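### In-session question-answering is stated only for the Sunset Without AIDS arm, so the comparison with the normal video mixes the film with live staff answers

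*Protocol article*

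**What the plan says.** All references are to the protocol article.

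- **Sunset Without AIDS intervention group.** A 25-minute film is shown once a week for 2 weeks. The section adds: "During the broadcast, a member of research team will be responsible for answering questions". It also says that "participants will be recognized and rewarded after completing two video viewing sessions and 2-week follow-up assessments".
- **Normal video group.** A 25-minute film from the Chinese CDC website, "which lacks a storyline and is not specifically aimed at older people". On matching: "Video length time and duration are the same as the *Sunset Without AIDS* group", with similar educational content. The section mentions neither a staff member answering questions nor a reward.
- **Lecture group.** "An AIDS expert will hold a health lecture on AIDS prevention", for 25 minutes once a week for 2 weeks, with similar content. Questions are not mentioned.
- **Table 2 (contamination and fidelity).** The comparators are equalised on content and time only.
- **Ancillary and post-trial care.** Participants' HIV-related questions will be answered during the trial. No arm is singled out, and this is not described as part of a session.
- **Discussion.** Comparing the Sunset and normal video groups is meant to show whether the Sunset film is attractive and "is better than a popular science propaganda video in improving" AIDS prevention ability.
- **Sample size and adherence.** Rewards are meant to help all 450 men keep to both the intervention and the follow-up: "Participants would receive some prizes for each assessment", plus 50 RMB for each man at the end.

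**The concern.** A comparison of two films supports a statement about the films only if the rest of the session is the same. Here the text gives one video arm a person who answers questions during the showing and gives the other video arm no such person. The primary outcome is a 10-item HIV knowledge questionnaire with one point per correct answer, so a staff member explaining transmission or condom use could raise the score whatever film is on the screen.

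The two components coincide completely by arm, so no adjustment or subgroup analysis can separate them afterwards. At stake is the meaning of the central contrast. A positive result could come from the film, from the live answers or from both, and the conclusion the Discussion has in view is about the film.

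**Working it through.** **Step 1. Set the arm descriptions side by side.**

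| Session feature | Sunset | Normal video | Lecture |
|---|---|---|---|
| Length and frequency | 25 min, weekly for 2 weeks | stated to be the same | 25 min, weekly for 2 weeks |
| Educational content | reference | similar | similar |
| Storyline, aimed at older people | yes | no | live expert, no film |
| Staff member answering questions in session | stated | not stated | not stated |

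The fourth row is a difference between the two video arms that the article does not list among its intended contrasts. The general offer under Ancillary and post-trial care reaches all arms, but it does not place anyone in the normal video sessions.

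**Step 2. The plan's own figures.** The article gives 135 per group for 80% power, raised to 150. The step to 150 fits 10% inflation: 135/(1 − 0.10) = 150. The 135 cannot be reproduced, because no effect size, SD or success rate is given. Solving backwards for a comparison of two means at two-sided alpha 0.05:

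d = (1.960 + 0.842) × √(2/135) = 2.802 × 0.1217 = 0.341 SD.

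This gives a scale: effects of about a third of an SD are what 135 per group would detect with 80% power.

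**Step 3. What a question-answering effect would do.** The documents give no size for it, so q = 0.1, 0.2 and 0.3 SD are assumptions. Suppose the film adds nothing and only question-answering acts. With 150 per arm, the standard error of the standardised difference is √(2/150) = 0.1155, and

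P(p < 0.05) = Φ(q/0.1155 − 1.960) + Φ(−q/0.1155 − 1.960).

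| Assumed q (SD) | q/0.1155 | Probability of p < 0.05 |
|---|---|---|
| 0 | 0 | 0.05 |
| 0.1 | 0.866 | 0.14 |
| 0.2 | 1.732 | 0.41 |
| 0.3 | 2.598 | 0.74 |

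**Step 4. Sensitivity to the planned Bonferroni correction.** The article does not say over how many tests it applies. Assuming three pairwise comparisons, alpha is 0.05/3 = 0.0167 and the critical value is 2.394. The same formula then gives 0.06, 0.25 and 0.58 for q = 0.1, 0.2 and 0.3, against 0.017 with no effect. The probabilities fall, but the pattern is the same.

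The calculation treats knowledge as a mean score. The Statistical analyses section calls it binary and plans chi-square tests, so these figures illustrate the order of size and do not predict the trial's own test.

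**The case against.** **Silence is not exclusion.** The Sunset section also carries procedures that apply to every arm, such as the repeat questionnaire after 2 weeks, and the other arm sections are shorter. A condensed article may have stated the question-answering once for all arms. This is the strongest point, and it means that the actual sessions may well be matched. It does not remove the problem. The normal video section says what is held equal to the Sunset arm, and in-session answers are not on that list. If they are given there too, the description of the comparator needs correcting.

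**Questions are answered for everyone.** The ancillary care statement softens the contrast, but it is not a session component. Table 2's recordings, central review and field checks would help to document differences, but they do not equalise the sessions.

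**The trial compares packages.** The second hypothesis ties the story to acceptability and feasibility, and the normal video section openly names a second difference, the target audience. This stands: the documents do not claim to isolate the storyline. The point here is narrower. Even the film as a whole is not isolated from staff answers.

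**Stronger readings that the documents do not support.** A reader might infer from "participants will be recognized and rewarded after completing two video viewing sessions and 2-week follow-up assessments" that only Sunset men are rewarded, that retention will therefore differ by arm, and that the dropout rule will turn this into a false advantage. But the Sample size and adherence section gives rewards to all 450 men for keeping to the intervention as well as the follow-up, and the Limitations section repeats that each person receives prizes. The reference to video viewing could also cover the normal video arm. No figure in the documents supports a difference in dropout. A reader might also extend the confounding to the lecture arm. That arm has a live expert and differs from Sunset in its whole mode of delivery, so that comparison never isolated the film.

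**Conclusion.** The point holds for Sunset versus normal video. As written, that comparison mixes the effect of the film with live question-answering on an outcome that such answers can raise directly. The size is unknown. Under the assumptions of no film effect, a question-answering effect of 0.1 to 0.3 SD, 150 analysed per arm and an uncorrected two-sided 5% test of means, the chance of a significant result is about 0.14 to 0.74 instead of 0.05.

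This should be corrected because it decides what the key comparison means, but it does not stop the trial from running. On the reward, all that remains is a request for clarification: the sentence appears only under the Sunset heading and should be tied to the trial-wide scheme.

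**What to change.** 1. Reconcile the three arm descriptions. State that the normal video arm has the same in-session question-answering as the Sunset arm and that the lecture arm has an equivalent opportunity, or that no arm has it.
2. If sessions have already differed, record by arm where questions were answered, and limit the conclusion to the film plus facilitated questions. This may be the branch that applies: enrolment began in June 2021 and recruitment was due to end in December 2021, before publication in February 2022.
3. Confirm in one sentence that the reward for completing sessions and the 2-week assessment is the trial-wide reward described under Sample size and adherence.

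For sessions still to come, the cost is a few sentences and a short instruction to session staff; Table 2 already has field team members confirming what each participant receives. For sessions already held, matching is no longer possible, and the cost is a record by arm and a narrower conclusion.
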